# Daily irradiation versus irradiation at two- to three-day intervals in stereotactic radiotherapy for patients with 1-5 brain metastases: study protocol for a multicenter open-label randomized phase II trial

**DOI:** 10.1186/s12885-022-10371-3

**Published:** 2022-12-05

**Keywords:** Brain metastases, Radiation biology, Stereotactic radiation, Treatment outcome, Clinical Trial, Phase II

## Abstract

**Background:**

Radiobiological daily changes within tumors are considered to be quite different between stereotactic radiotherapy (SRT) (e.g., 50 Gy in 4 fractions) and conventional radiotherapy (e.g., 60 Gy in 30 fractions). We aim to assess the optimal interval of irradiation in SRT and compare outcomes of daily irradiation with irradiation at two- to three-day intervals in SRT for patients with one to five brain metastases (BM).

**Methods:**

This study is conducted as a multicenter open-label randomized phase II trial. Patients aged 20 or older with one to five BM, less than 3.0 cm diameter, and Karnofsky Performance Status ≥70 are eligible. A total of 70 eligible patients will be enrolled. After stratifying by the number of BMs (1, 2 vs. 3–5) and diameter of the largest tumor (< 2 cm vs. ≥ 2 cm), we randomly assigned patients (1:1) to receive daily irradiation (Arm 1), or irradiation at two- to three-day intervals (Arm 2). Both arms are performed with total dose of 27-30 Gy in 3 fractions. The primary endpoint is an intracranial local control rate, defined as intracranial local control at initially treated sites. We use a randomized phase II screening design with a two-sided α of 0∙20. The phase II trial is positive with *p* < 0.20. All analyses are intention to treat. This study is registered with the UMIN-clinical trials registry, number UMIN000048728.

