### Secondary endpoints

Intracranial progression-free survival (IC-PFS), defined as intracranial PFS at initially treated and at new sites.OS, defined as the time from the date of randomization to death from any cause.Toxicity, assessed by the National Cancer Institute Common Terminology Criteria for Adverse Events (CTCAE) version 5.0.Non-worsening of Karnofsky performance status (KPS), defined as the time from randomization to decline of KPS from any cause.Non-worsening of mini mental status examination (MMSE), defined as the time from randomization to decline of MMSE from any cause.

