### Interventions

Arm 1: consecutive daily irradiation; total SRT duration, 3 days.

Arm 2: irradiation at two- to three-day intervals; total SRT duration, 8 days.

Both arms are performed once a daily with total dose of 27-30 Gy in 3 fractions (9-10 Gy per fraction). The prescription dose to the PTV is 30 Gy in 3 fractions for tumors ≤2.0 cm and 27 Gy in 3 fractions for tumors > 2.0 cm.

All patients were immobilized in a spine position with the head fixed with a shell and simulated by CT with less than 2.0-mm slice thickness. All targets and organs at risk (OAR) are contoured on the RT planning system. The CT images are fused with MRI for delineation of the target and OAR. The gross tumor volume (GTV) includes an enhancing area of the contrast agent on MRI. The clinical target volume (CTV) is defined as the same as the GTV. The GTV is expanded symmetrically by 0-2.0 mm in all dimensions to create the planning treatment volume (PTV). The margin between the GTV and PTV depends on the discretion of the medical physicist in each participating institution. OAR include the eyeball, inner ear, and the brain stem, chiasma, optic nerve, and spinal cord is expanded symmetrically by 2.0 mm in all dimensions to create the planning risk organ (PRV) if these OAR are close to the PTV. The plan is created to achieve a target coverage with 95% (D95%) of the PTV receiving 100% of each prescription dose, and to provide as homogenous of a dose distribution as possible within the target (D1% < 120% of each prescription dose, D99% > 90% of each prescription dose). The dose constraint of all OAR and PRV is the maximum dose < 20 Gy. When sufficient coverage of the PTV was not achieved without deviation from the dose constraint for the OAR and PRV, the reduction of prescription dose to the acceptable range were allowed. The patient is necessarily treated using image-guided RT such as a megavoltage- or kilovoltage-CT or ExacTrac system acquired on the RT unit immediately before irradiation.

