### Sample size

We use a randomized phase II screening design, with a two-sided α of 0.20 and a power of 80% as recommended for our current study [12]. In a phase II screening design, the α level is set higher than the level of a phase III design (i.e., 0.05). Even if the phase II trial is positive (i.e., *p* < 0.20), that is not considered conclusive without a subsequent phase III trial. The results of the previous study of irradiation at intervals demonstrated a 1-year IC-LC of 93% [13]. Assuming a 1-year IC-LC of 70% for Arm 1 (consecutive daily irradiation) and 90% for Arm 2 (irradiation at two- to three-day intervals) and a 1-year OS of 50% for target patients, with 80% power, alpha of 0.20, an 5% lost follow-up rate, accrual time of 4 years and a total trial time of 5 years, 70 patients will be required (35 in Arm 1 and 35 in Arm 2). The secretariat of the study will contact all co-investigators to facilitate enrollment regularly.

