### Primary endpoint

The intention-to-treat analyses will be performed, and patients will be analyzed in the groups to which they are assigned. The IC-LC rate will be calculated using the Kaplan-Meier method and differences will be compared using the stratified log-rank test. Only recurrence of initially treated sites will be treated as event and death will not be considered to be competing event. When enrolled patient dies, the data at the last follow up will be used to calculate the IC-LC rate. Cox proportional hazards multivariable regression analysis will be used to determine baseline factors predictive of primary endpoint.

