### Secondary endpoints

The IC-PFS rate will be calculated using the Kaplan-Meier method and differences will be compared using the stratified log-rank test. Only development of initially treated sites and new BM will be treated as event and death will not be considered to be competing event. When enrolled patient dies, the data at the last follow up will be used to calculate the IC-PFS rate. The OS rate will be calculated using the Kaplan-Meier method and differences will be compared using the stratified log-rank test. OS was defined as the time from the date of randomization to death from any cause.

The rates of grade 2 or higher toxicity will be compared between groups using the Fisher’s Exact Test. The non-worsening of KPS and MMSE scores at 6- and 12-months post-enrollment will be measured with differences between groups tested using the Fisher’s Exact Test. When enrolled patient dies, the data at the last follow up will be used. For KPS, a decrease in KPS of ≥10% will be considered a decline in KPS and sensitivity analysis will be performed. For MMSE, a decrease in MMSE score of ≥3 points will be considered a decline in cognitive function and sensitivity analysis will be performed.

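### The intention-to-treat rule as published also covers the toxicity comparison and would tend to dilute a true difference between schedules; a minor point with a cheap remedy

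*Protocol article*

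**What the plan says.** Three places in the protocol article bear on this.

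- Abstract, Methods: "All analyses are intention to treat". No endpoint is exempted.
- Statistical analysis, Primary endpoint: "The intention-to-treat analyses will be performed, and patients will be analyzed in the groups to which they are assigned". This gives the meaning of the rule, but under the heading of the primary endpoint.
- Statistical analysis, Secondary endpoints: "The rates of grade 2 or higher toxicity will be compared between groups using the" Fisher's exact test. No treated-patient or as-received population is named.

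Toxicity is a listed secondary endpoint: "Toxicity, assessed by the National Cancer Institute Common Terminology Criteria for Adverse Events (CTCAE) version 5.0". The regimens share total dose and number of fractions and differ in spacing: "Arm 1: consecutive daily irradiation; total SRT duration, 3 days" against "Arm 2: irradiation at two- to three-day intervals; total SRT duration, 8 days". The planned size is "70 patients will be required (35 in Arm 1 and 35 in Arm 2").

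**The concern.** For a superiority question on local control, analysis by assigned arm is the cautious choice: patients who do not follow their assignment make a false claim of benefit less likely. For toxicity the same shrinkage favours a finding of no difference.

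Two kinds of patient matter. One receives the other arm's schedule and carries that schedule's toxicity into the assigned arm. The other is randomized but never irradiated, cannot have treatment-related toxicity, and still counts in the denominator. The article allows up to 14 days between randomization and the start of treatment, so untreated patients are possible.

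The article says that it will assess the effect of the SRT interval on toxicity. That question is about the interval delivered, and a comparison by assignment answers it less directly.

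**Working it through.** The plan has no toxicity figure to reproduce: it gives no expected grade 2 or higher rate, no switching rate and no significance level for this test. The stated design values, "with a two-sided α of 0.20 and a power of 80"%, belong to the primary endpoint. The rates below are therefore assumptions.

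**Inputs.** n = 35 per arm (Sample size section) and Fisher's exact test (Secondary endpoints). Assumed: true rates p1 (less toxic schedule) and p2 (more toxic schedule); shares c1 and c2 of the two arms that receive the other schedule, unrelated to risk.

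**Dilution from switching.** The expected rates by assignment are

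- less toxic arm: (1 − c1)·p1 + c1·p2
- more toxic arm: (1 − c2)·p2 + c2·p1

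so the difference by assignment is (1 − c1 − c2)·(p2 − p1). It moves toward zero for any positive share (with c1 + c2 below 1).

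**Dilution from untreated patients.** If a share u of each arm is never irradiated and has no SRT toxicity, the difference becomes (1 − u)·(p2 − p1). With u = 5% and 10% vs 40%, the rates are 9.5% and 38%, and the difference is 28.5 points instead of 30. This direction needs similar shares in the two arms. If untreated patients fall only in the less toxic arm, the apparent difference grows slightly.

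**Power.** Exact, by enumerating both binomials with 35 per arm, at two-sided 0.05:

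| True rates | Switching | Rates by assignment | Difference (points) | Power |
|---|---|---|---|---|
| 10% vs 40% | none | 10.0% vs 40.0% | 30.0 | 0.785 |
| 10% vs 40% | 5%, less toxic arm only | 11.5% vs 40.0% | 28.5 | 0.721 |
| 10% vs 40% | 5%, more toxic arm only | 10.0% vs 38.5% | 28.5 | 0.744 |
| 10% vs 40% | 5% in each arm | 11.5% vs 38.5% | 27.0 | 0.675 |
| 10% vs 30% | none | 10.0% vs 30.0% | 20.0 | 0.455 |
| 10% vs 30% | 5% in each arm | 11.0% vs 29.0% | 18.0 | 0.367 |
| 10% vs 20% | none | 10.0% vs 20.0% | 10.0 | 0.129 |
| 10% vs 20% | 5% in each arm | 10.5% vs 19.5% | 9.0 | 0.106 |

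One arm of 35 at 5% is 0.05 × 35 = 1.75, or about two patients. One switched patient in the less toxic arm (c1 = 1/35) gives 0.75 for 10% vs 40%.

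**Which pattern is plausible.** Arm 1 lasts 3 days and Arm 2 lasts 8. An interruption lengthens a course, so it can move an Arm 1 patient toward the longer schedule. It cannot turn an 8-day course into three consecutive days. The one-arm rows therefore fit better than the two-arm rows, and even they assume a full switch, whereas a one-day slip gives only an intermediate course. The article does not say which schedule would be the more toxic, so both one-arm rows are shown.

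**The case against.** The strongest reply is that the textual basis is thin. The word that extends the rule to every analysis stands in one abstract sentence; the body states the rule only under the primary endpoint, and a safety population is commonly defined in a full protocol or analysis plan that is not shown here. This lowers the weight but does not remove the point. The published sentence is a positive rule, not a gap, and a safety population defined elsewhere would contradict it.

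The second reply is that sample size limits this comparison far more than the analysis population does. That stands. At 10% vs 30%, power is 0.46 with no switching at all, and at 10% vs 20% it is 0.13.

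The third is that grouping by schedule received gives up part of the protection of randomization. If schedules change because patients become unwell, the bias can run either way. That also stands, and it is why the as-assigned comparison has to be kept.

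A reader might go further and infer that 5–10% of patients in each arm will switch fully, taking power for 10% vs 40% down to 0.68 or 0.55. The documents do not support this: they give no switching rate, and full switching in both directions does not fit the two course lengths. A reader might also take the list of items monitored by the data monitoring committee as evidence that schedule switches are expected. Protocol deviation is a generic item there and says nothing about switching. Serious adverse events are on the same list, so safety oversight does not rest on this one test.

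**Conclusion.** The point holds as a minor one. Under the published wording, grade 2 or higher toxicity is compared by assigned arm among all randomized patients, which in general dilutes a true difference between schedules. The size cannot be fixed from the documents and is probably small. Under an assumed 10% vs 40% and 5% switching in one arm only, power at 0.05 falls from 0.79 to about 0.72–0.74.

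That illustration rests on a 30-point difference that nothing in the article suggests, a 0.05 level that the article does not set for toxicity, full rather than partial switching, and switching unrelated to risk. With no switched and no untreated patients, the two groupings coincide. It would go too far to conclude that the trial is likely to miss a safety signal because of this rule.

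**What to change.** 1. In the abstract, limit the statement to efficacy: *All efficacy analyses are intention to treat.*
2. In Secondary endpoints, state that grade 2 or higher toxicity is reported among patients who received at least one fraction, grouped by schedule actually received, with the as-assigned comparison always shown beside it.
3. Set in advance an analysis rule for classifying intermediate and incomplete courses. Without it, grouping by schedule received is undefined for the likeliest deviations.
4. Confirm that fraction dates are captured. The Quality assurance section says that centres send SRT information for each patient but does not say that this includes the date of each fraction.

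The cost is a few sentences of analysis wording and possibly one data field; sample size and treatment are untouched. The downside is that the as-received table is not fully protected by randomization, so a disagreement between the two tables should be interpreted with caution and not settled automatically in favour of either.

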**Discussion:**

This study will provide an assessment of the impact of SRT interval on local control, survival, and toxicity for patients with 1–5 BM. The trial is ongoing and is recruiting now.

**Trial registration:**

UMIN000048728. Date of registration: August 23, 2022.

https://center6.umin.ac.jp/cgi-bin/ctr/ctr_view_reg.cgi?recptno=R000055515.

## Background

Stereotactic radiotherapy (SRT) has improved clinical outcomes for several types of cancers or metastatic lesions [1–4]. A recent trial suggests that when all sites of disease are treated with SRT in patients with oligometastatic disease, this therapeutic strategy can improve overall survival (OS) [5]. SRT is characterized by the use of hypofractionation and much higher doses per fraction (e.g., 50 Gy in 4 fractions) than conventional radiotherapy (RT), which is performed every weekday with multiple fractions using low doses per fraction (e.g., 60 Gy in 30 fractions). Figure 1 shows the concise description for the practical difference between the two methods.

**Fig. 1 Fig1:**
[figure not shown]
Comparison of practical difference between conventional radiotherapy (RT) and stereotactic radiotherapy (SRT) (e.g., early-stage lung cancer)

Most tumors have hypoxic tumor cells which are radioresistant [6] and can cause a recurrence after RT [7, 8]. During the period of daily irradiation, surviving hypoxic cells within tumor reoxygenate and get more sensitive to successive irradiation [9, 10]. We previously investigated the variations in the percentage of hypoxic cells after single high-dose irradiation in the murine tumors [11]. As the decrease of the hypoxic fractions continued at least 72 hours after single high-dose irradiation, we consider that reoxygenation continues more than 3 days after single high-dose irradiation. Thus, when SRT is performed on a daily basis, the benefit of reoxygenation can be reduced owing to the use of high-dose irradiation at insufficient intervals. We think that longer intervals more than 24-hour may be necessary to allow more reoxygenation to occur and enhance therapeutic efficacy of SRT.

In this multicenter open-label randomized phase II trial, we aim to assess the optimal interval of SRT and compare outcomes of daily irradiation with irradiation at two- to three-day intervals for patients with one to five brain metastases (BM).

## Methods/design

Participating institutions will be six academic and four general hospitals in Japan. In each participating institution, the institutional review board (IRB) will approve the protocol before patient enrollment occurred. The study was started in September 2022, and participant enrollment will be between September 2022 and March 2026. This trial has been registered with the UMIN-clinical trials registry (UMIN-CTR: UMIN000048728, Date of registration: August 23, 2022, Version 1.0).

### Primary endpoint

Intracranial local control rate (IC-LC), defined as intracranial local control at initially treated sites.

### Secondary endpoints

Intracranial progression-free survival (IC-PFS), defined as intracranial PFS at initially treated and at new sites.OS, defined as the time from the date of randomization to death from any cause.Toxicity, assessed by the National Cancer Institute Common Terminology Criteria for Adverse Events (CTCAE) version 5.0.Non-worsening of Karnofsky performance status (KPS), defined as the time from randomization to decline of KPS from any cause.Non-worsening of mini mental status examination (MMSE), defined as the time from randomization to decline of MMSE from any cause.

### Study design

The study is conducted as a multicenter open-label randomized control phase II trial. Patients will be randomized in a 1:1 ratio between consecutive irradiation (Arm 1) vs. irradiation at intervals (Arm 2) to BM. Patients will be stratified by (1) maximum diameter (≤ 2 cm vs. > 2 cm) among their BM and (2) number of BM (1, 2 vs. 3-5). Figure 2 shows the study schema.

**Fig. 2 Fig2:**
[figure not shown]
Study schema. MRI: magnetic resonance imaging; KPS: Karnofsky performance status; MMSE: mini mental status examination; JCS: Japan Coma Scale

### Inclusion criteria

Age 20 years or older.KPS ≥ 70.Total number of 1-5 BM by contrast-enhanced magnetic resonance imaging (MRI).BM with less than 3.0 cm diameter by contrast-enhanced MRI.Willing to provide informed consent.

### Exclusion criteria

Histological type of the primary site is lymphoma, small cell lung cancer, and germ cell tumor.Metastases of the brainstem.Meningeal carcinomatosis.History of whole brain radiation therapy (WBRT) or substantial overlap with a previously treated radiation volume.Surgical history for BM.Difficult to be enrolled to the study by reason of insanity.Inability to use enhancing agent for MRI due to low renal function or allergy.In pregnancy or with expectation of pregnancy.Physician dismiss as subject of the study.

### Pre-treatment evaluation

Re-staging is performed within 8 weeks prior to randomization. ^18^F-fluorodeoxyglucose (18-FDG) positron emission tomography (PET) -computed tomography (CT) or a contrast-enhanced CT of the neck to the pelvis is recommended for the evaluation of extracranial metastases. In cases where a contrast agent is unavailable due to impaired renal function or allergic intolerance, a plain CT is allowed. Before random assignment within 2 weeks, all patients are necessary to be evaluated by an MRI of the brain. MRI is performed with a gadolinium-enhanced T1 3D Fast Field Echo and 3D reconstruction of the axial, sagittal, and coronal planes with 1 mm slice thickness (thin-slice MRI). In addition, each patient undergoes a baseline evaluation consisted of medical history including prior treatments of cancer and concomitant anticancer medications, symptom burden, KPS, Japan Coma Scale (JCS), and MMSE.

### Interventions

Arm 1: consecutive daily irradiation; total SRT duration, 3 days.

Arm 2: irradiation at two- to three-day intervals; total SRT duration, 8 days.

Both arms are performed once a daily with total dose of 27-30 Gy in 3 fractions (9-10 Gy per fraction). The prescription dose to the PTV is 30 Gy in 3 fractions for tumors ≤2.0 cm and 27 Gy in 3 fractions for tumors > 2.0 cm.

All patients were immobilized in a spine position with the head fixed with a shell and simulated by CT with less than 2.0-mm slice thickness. All targets and organs at risk (OAR) are contoured on the RT planning system. The CT images are fused with MRI for delineation of the target and OAR. The gross tumor volume (GTV) includes an enhancing area of the contrast agent on MRI. The clinical target volume (CTV) is defined as the same as the GTV. The GTV is expanded symmetrically by 0-2.0 mm in all dimensions to create the planning treatment volume (PTV). The margin between the GTV and PTV depends on the discretion of the medical physicist in each participating institution. OAR include the eyeball, inner ear, and the brain stem, chiasma, optic nerve, and spinal cord is expanded symmetrically by 2.0 mm in all dimensions to create the planning risk organ (PRV) if these OAR are close to the PTV. The plan is created to achieve a target coverage with 95% (D95%) of the PTV receiving 100% of each prescription dose, and to provide as homogenous of a dose distribution as possible within the target (D1% < 120% of each prescription dose, D99% > 90% of each prescription dose). The dose constraint of all OAR and PRV is the maximum dose < 20 Gy. When sufficient coverage of the PTV was not achieved without deviation from the dose constraint for the OAR and PRV, the reduction of prescription dose to the acceptable range were allowed. The patient is necessarily treated using image-guided RT such as a megavoltage- or kilovoltage-CT or ExacTrac system acquired on the RT unit immediately before irradiation.

### Quality assurance for SRT

Each participating centre is required to send the SRT information of each enrolled patient to the principal investigator. The principal investigator will check the SRT data throughout the trial period and will inform each participating centre if needed.

### Systemic therapy

Patients treated with prior systemic therapy are eligible for this study. Chemotherapy treatment are not allowed during the period of SRT, but hormonal therapy and drugs for brain edema (e.g., steroid and/or glycerol) are allowed for patients with symptom burden. The enrolled patients can receive systemic therapy after SRT.

